**LIST OF ABBREVIATIONS AND RELEVANT DEFINITIONS**

|                |                                                                                                                                                                                                                                                                                                                                                  |
|----------------|--------------------------------------------------------------------------------------------------------------------------------------------------------------------------------------------------------------------------------------------------------------------------------------------------------------------------------------------------|
| BBS     | Berg Balance Scale                                                                                                                                                                                                                                                                                                                        |
| BI      | Barthel Index                                                                                                                                                                                                                                                                                                                             |
| CME     | Caregiver mediated exercise                                                                                                                                                                                                                                                                                                               |
| CBO     | Centraal begeleidings orgaan                                                                                                                                                                                                                                                                                                              |
| CSI     | Caregiver strain index                                                                                                                                                                                                                                                                                                                    |
| ESO     | European Stroke Organisation                                                                                                                                                                                                                                                                                                              |
| ESD     | Early Supported Discharge                                                                                                                                                                                                                                                                                                                 |
| FAC     | Functional Ambulation Categories                                                                                                                                                                                                                                                                                                          |
| FAME    | Family mediated exercises                                                                                                                                                                                                                                                                                                                 |
| HADS    | Hospital anxiety and depression scale                                                                                                                                                                                                                                                                                                     |
| HSU     | Hospital Stroke Unit                                                                                                                                                                                                                                                                                                                      |
| LOS     | Length of Stay                                                                                                                                                                                                                                                                                                                            |
| METC    | Medical research ethics committee (MREC); in Dutch: medisch ethische toetsing commissie (METC)                                                                                                                                                                                                                                            |
| MMSE    | Mini Mental State Evaluation                                                                                                                                                                                                                                                                                                              |
| NEADL   | Nottingham Extended ADL index                                                                                                                                                                                                                                                                                                             |
| NH      | Nursing Home                                                                                                                                                                                                                                                                                                                              |
| PT      | Physical Therapist                                                                                                                                                                                                                                                                                                                        |
| RC      | Rehabilitation Centre                                                                                                                                                                                                                                                                                                                     |
| RCT     | Randomized controlled trial                                                                                                                                                                                                                                                                                                               |
| RMI     | Rivermead Mobility Index                                                                                                                                                                                                                                                                                                                  |
| (S)AE   | (Serious) Adverse Event                                                                                                                                                                                                                                                                                                                   |
| SIS     | Stroke impact scale                                                                                                                                                                                                                                                                                                                       |
| Sponsor | The sponsor is the party that commissions the organisation or performance of the research, for example a pharmaceutical company, academic hospital, scientific organisation or investigator. A party that provides funding for a study but does not commission it is not regarded as the sponsor, but referred to as a subsidising party. |
| WHO     | World Health Organisation                                                                                                                                                                                                                                                                                                                 |
| WMO     | Medical Research Involving Human Subjects Act (in Dutch: Wet Medisch-wetenschappelijk Onderzoek met Mensen)                                                                                                                                                                                                                               |

## SUMMARY

### Rationale:

Several systematic reviews have indicated that additional exercise therapy and repetitive task training have a significant effect on functional outcome after stroke. Guidelines therefore conclude that patients in a rehabilitation setting should have the opportunity to get an increase of intensity of therapy. At this moment resources in rehabilitation facilities are not sufficient to meet these recommendations. A new method could be to involve caregivers (partner, family, friends) in exercise training. Previous studies suggest that this form of exercises done with a caregiver can lead to a better functional outcome for the patient and less strain for the caregiver. A critical part will be safety, adherence of the patient and caregiver and continuing support, for which innovative e-health and structured tele-rehabilitation services could be used.

In addition, a recent meta-analysis has shown that early supported discharge with additional services in the community is beneficial for optimizing the transition from the rehabilitation setting to the home situation and is cost-effective by reducing the length of stay of inpatient services, acknowledging that inpatient rehabilitation accounted for about 44% of all care of stroke costs.

**Objective:** The primary aim of this study is to evaluate the feasibility, clinical effectiveness and cost effectiveness of a caregiver mediated exercises programme combined with e-health services (CARE4STROKE) to improve self-reported health status and reduce the length of stay and costs by allowing early supported discharge of stroke patients to their own home setting.

**Study design:** randomized controlled trial (RCT).

**Study population:** 66 stroke patients and their caregivers, admitted in several rehabilitation centers, Hospital Stroke Units and nursing homes in the Netherlands will participate in this study.

**Intervention:** Participants will be randomly allocated to either 8 weeks of the CARE4STROKE programme in addition to usual care or to 8 weeks of usual care.

### Main study parameters/endpoints:

Primary measurements of outcome: 1) Length of Stay and 2) self-reported health-status with the Stroke Impact Scale (SIS version 3.0). Secondary outcomes for included stroke patients are EuroQol-5D (EQ-5D), the Barthel Index, Rivermead Mobility Index, Berg Balance Scale, 5 meter walking speed, 6 minute walking test, Timed Up and Go Test, the Motricity Index (leg), The Fugl-Meyer assessment (leg), Nottingham Extended Activities of Daily Living and modified Rankin Scale. In order to track the daily activity, patients will wear a wireless activity monitor on the wrist one week before and after the intervention. In addition, patients keep a

diary to record adherence to the exercise program and emerging complications. Caregiver burden will be evaluated with the Caregiver Strain Index and Carer Quality of Life Index. For patients and caregivers the Hospital Anxiety and Depression Scale, Fatigue Severity Scale, General self-efficacy scale and Personal Opinion Questionnaire for empowerment will be used. In addition each couple will use a cost diary.

**Nature and extent of the burden and risks associated with participation, benefit and group relatedness:** Participants in the intervention group get a surplus of 150 minutes of exercise training a week; Caregivers will be involved and will need to allocate time to the programme as well. Care is taken to assure safe performance of the exercises. This will be accomplished by e-health and tele-rehabilitation services and safety instructions and close guidance and coaching of a therapist. The control group will have no additional benefit or risks. Assessments will take place at baseline, after the intervention and at twelve weeks follow up. They consist of questionnaires and tests, taking approximately two hours per assessment.

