Recently, Gregory et al. recommended a crucial role of e-Health and ICT support for the coordination of caregiver-mediated interventions. However, none of the existing studies however have combined e-Health services with Caregiver Mediated Exercise to enhance Early Supported Discharge. .

The present type I cost-effectiveness study will serve as basis for a future cluster stepped-wedge randomized phase III clinical trial to investigate the cost-effectiveness of the CARE4STROKE program, in which Caregiver Mediated Exercise is combined with e-Health services aimed at Early Supported Discharge

We hypothesize that the CARE4STROKE program will:

- 1) be feasible and safe to execute;
- 2) allows ESD of patient to their own home setting with a significant reduced inpatient stay of 1 day for HSU and 7 days for RC/NH.
- 3) increase patients self-reported health status with concomitant reduced levels of caregiver burden and
- 4) enhance feelings of empowerment as perceived by patient and partner when compared to usual care..

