## 2. OBJECTIVES

The CARE4STROKE program is directed at improving self-reported health status and reduce LOS and costs by allowing ESD of stroke patients to their own home setting. ESD from setting of admission will be enhanced by: 1) starting CME applied by a PT focused on gait and gait-related activities immediately after admission in a HSU, RC NH and 2) continuous weekly support by a PT in patients own home setting after discharge with support of e-Health services. The e-Health services will contain the following package: 1) an app with CME for 8 weeks, starting immediately after admission; 2) telerehabilitation services allowing instructions of the PT including monitoring progress of patients and adherence of caregiver and 3) telephone and video conferencing based counseling and weekly visits by a coordinating PT from the setting of discharge focused on increasing feelings of empowerment and self-management of the caregiver.

The main aim of the present pilot study is to investigate feasibility, clinical effectiveness and cost-effectiveness of a caregiver-mediated exercise program (CARE4STROKE) combined with e-Health services, to be evaluated in terms of self-reported health status and mean LOS in stroke patients who are admitted at a HSU, RC or NH and discharged to their own home setting, as compared to usual care.

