#### **4.3 Sample size calculation**

We expect a significant reduction of 5 points (11%) on the SIS mobility domain  [ mean 79,4, sd 14] in favor of the experimental training group. We expect that minimally 30 patients are required per arm of the trial. Including 10% dropouts, we suppose that a minimum of 66 stroke patients, (i.e. 22 per centre), are needed to achieve a sufficient statistical power of 80% using a significance level alpha of  $p < 0.05$ .

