## 6. METHODS

### 6.1 Study parameters/endpoints

#### 6.1.1 Main study parameters

For the patient:

- 1) Length of Stay in the HSU, RC or NH, defined as the moment of admittance-moment of discharge. (primary outcome)
- 2) Self reported health status with the Stroke Impact Scale (SIS version 3.0) 
- 3) Quality of life, measured with the EQ-5D. 
- 4) Mobility, measured by the Rivermead mobility index (RMI) 
- 5) Independence in performing basic activities of daily living, measured by the Barthel index (BI) 
- 6) Walking ability, assessed with the 5 metre walking speed, the 6 minute walking test and the timed up and go test (TUG). 
- 7) Extended Activities of daily living, measured by the Nottingham extended ADL (NEADL). 
- 8) Functional outcome, measured by Modified Rankin Scale (MRS) dichotomised to good outcome (0-2) or poor outcome (3-6). 
- 9) Balance, assessed with the Berg Balance Scale (BBS) 
- 10) Selectivity lower extremity, assessed with the Fugl Meyer (FM) lower extremity. 
- 11) Strength of the lower limb, assessed with the Motricity Index (MI). 
- 12) The amount of daily activity, assessed with a comfortable and wireless activity monitor on the wrist.

For the caregiver:

- 13) the experienced strain of the caregiver measured by the Expanded Caregiver strain index. (CSI +) 
- 14) Quality of life, measured with the CareQOL. 

For both:

- 15) Amount of (additional) practice done by the couples in the intervention and controlgroup, this will be measured with a diary (see appendix) Problems and adverse events like falls will also be recorded in the diary
- 16) Personal Opinion Questionnaire for empowerment .

- 17) Emotional functioning, measured with the Hospital Anxiety and Depression Scale (HADS).
- 18) Fatigue, measured by the fatigue severity scale.
- 19) Self-efficacy, measured by the general self-efficacy scale.
- 20) A cost diary, comprising questions on items such as consultation with neurologists, family doctors, paramedics, re-admission to hospitals or rehabilitation centres, drug use, home care and non-professional support.

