### 8.3 Cost-effectiveness analysis

A cost effectiveness and a cost-utility analysis will be performed The primary outcome of the trial, length of Stay, in combination with the information of the cost diary will be used in the cost effectiveness analysis. Unit costs will be taken from national sources.

In the costs utility-analysis the outcome measure is quality-adjusted life-years (QALYs) based on the Dutch tariff for the Euro(QoI).

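### The protocol names its primary outcome inconsistently (length of stay plus SIS, or length of stay alone), and its only power statement concerns the SIS mobility domain, so the stated 80% does not apply to length of stay

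*Protocol*

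**What the plan says.** Five places in the protocol bear on which outcome decides the trial.

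- **Summary, main study parameters/endpoints:** two primaries, "Primary measurements of outcome: 1) Length of Stay and 2) self-reported health-status with the Stroke Impact Scale (SIS version 3.0". EQ-5D, Barthel Index, Rivermead Mobility Index and most other measures are called secondary there.
- **Section 2:** the main aim is "to be evaluated in terms of self-reported health status and mean LOS in stroke patients", so both outcomes carry it.
- **Section 6.1.1:** twenty main study parameters. Only the first is labelled primary: "Length of Stay in the HSU, RC or NH, defined as the moment of admittance-moment of discharge. (primary outcome". SIS is second, without the label.
- **Section 8.3:** in the singular, "The primary outcome of the trial, length of Stay, in combination with the information of the cost diary".
- **Section 4.3:** "We expect a significant reduction of 5 points (11%) on the SIS mobility domain", with mean 79.4 and SD 14, then "We expect that minimally 30 patients are required per arm of the trial". With 10% dropout this becomes 66 patients, at 80% power and alpha 0.05.

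Section 1 hypothesises for LOS a "significant reduced inpatient stay of 1 day for HSU and 7 days for RC/NH" (HSU: hospital stroke unit; RC: rehabilitation centre; NH: nursing home). No SD for LOS appears anywhere. Section 8.2 compares the 6.1.1 outcomes by multilevel regression at the different time points, with location in the model, and does not rank them.

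**The concern.** A reader cannot tell from the protocol whether SIS is primary. If it is, the deciding score (a domain or a summary) and the deciding visit (8 or 12 weeks) are not given, nor is it stated whether one positive outcome suffices. The basis for claiming success could then be settled after the results are known.

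The second problem is a mismatch. The one stated power figure belongs to a SIS domain, while the outcome that the Summary, 6.1.1 and 8.3 all call primary was never sized. Someone reading the 80% as the trial's power for its primary outcome would be misled.

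**Working it through.** **1. The statements side by side**

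| Place | LOS | SIS |
|---|---|---|
| Summary | primary | primary; no score, visit or either/both rule |
| 2 | in the main aim | in the main aim |
| 6.1.1 | primary | listed, not labelled primary |
| 8.3 | primary, singular | not mentioned |
| 4.3 | not mentioned | mobility domain is the basis for N |

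These are two incompatible statements of the primary outcome, plus a sample size built on something neither of them specifies.

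**2. The plan's own figure**

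Inputs from 4.3: difference 5, SD 14, alpha 0.05 (taken as two-sided), power 80%.

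n per arm = 2 × (1.960 + 0.842)² × 14² / 5² = 123.1, so 124, not 30. One-sided it is 97. At 30 per arm the power is Φ(5/14 × √15 − 1.960) = Φ(1.383 − 1.960) = 28%. The dropout step does reproduce: 60 × 1.1 = 66. The shortfall is a separate matter. What counts here is that the calculation concerns SIS mobility and contains no LOS input.

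**3. What LOS could support**

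No LOS power can be computed without an SD, but the largest SD compatible with 80% power can. By the normal formula, the detectable standardised difference with 30 per arm is √(2/30) × 2.802 = 0.723. With the t distribution it is 0.736.

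- 7 days: 7 / 0.736 = 9.5 days (9.7 by the normal formula).
- Average of the hypothesised effects over three equal centres: (1 + 7 + 7)/3 = 5 days, giving 5 / 0.736 = 6.8 days.

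The 7-day figure is the more favourable one, because 7 days is hypothesised only for RC and NH. For illustration, with 30 per arm, a 7-day effect and **assumed** SDs of 10, 14, 20 and 30 days, power by the normal formula is 77%, 49%, 27% and 15%.

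**4. Type I error if both are primary**

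Assumptions: two tests, each at 0.05, success on either.

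- Independent: 1 − 0.95² = 9.75%.
- Correlation 0.3, 0.5, 0.7, 0.9 (bivariate normal): 9.5%, 9.1%, 8.3%, 7.0%.
- LOS alone primary, or both required: no more than 5%.

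**5. Cost of splitting alpha**

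At 0.025 for SIS mobility: 2 × (2.241 + 0.842)² × 14² / 5² = 149.04, so 150 per arm. With 30 per arm the power is Φ(1.383 − 2.241), about 19.5%.

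**The case against.** Several points on the other side are fair.

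- **Section 4.3 does not call SIS mobility primary**, and the domain is part of the SIS 3.0 that the endpoint lists include. That stands: it is a sizing mismatch, not a third definition of the primary outcome.
- **A multiplicity rule may sit in a statistical analysis plan that is not shown.** Its absence from the protocol is therefore no finding. But which outcome is primary is a matter the protocol itself answers, and it answers it in two ways.
- **The trial is called a pilot for a later phase III trial.** This softens the confirmatory argument. It does not remove it, because the protocol states a power, a significance level and an aim of clinical effectiveness.

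Three stronger readings may tempt a reader, and the document does not support them.

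- *That alpha is 0.05 for every outcome.* The level is written in 4.3 for the sizing and in 8.1, which deals with baseline comparisons. Section 8.2 gives none. Applying 0.05 to each outcome is an inference from its being the only level stated.
- *That twenty main parameters give a 64% chance of a false positive (1 − 0.95²⁰).* The Summary calls most of them secondary, two are diaries, and several measure overlapping aspects of mobility and daily activities, so independence is not credible.
- *That the setting-specific LOS effects cannot be shown with 22 patients per centre.* No LOS SD is given, so this is unproven. RC and NH together make 44 patients, and section 1 states a hypothesis; no separate test by setting is planned.

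**Conclusion.** The protocol contradicts itself on the primary outcome and attaches its only power claim to a SIS domain that no section designates as primary. This rests on the text alone.

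LOS has a hypothesised effect but no SD and no power, so the 80% cannot be read as applying to it. Whether the trial is underpowered for LOS is unknown. The SD ceilings of about 9.5 days (7-day effect) and 6.8 days (5-day average) assume 30 evaluable patients per arm, a two-sided 0.05 test and roughly normal data.

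The error inflation is conditional. It reaches 9.75% at most, or about 7 to 9.5% with correlated outcomes, and only under an either-outcome rule at 0.05 each, which the protocol does not state. The inconsistency should be settled before analysis, because it determines what the trial may conclude.

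**What to change.** Put one statement in the Summary, 4.3, 6.1.1 and 8.3.

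1. **Primary:** LOS, pooled over settings and adjusted for location (already in the 8.2 model), as 6.1.1 and 8.3 imply.
2. **Key secondary:** one named SIS score at one named visit, for example mobility at 8 weeks, tested only if LOS is significant.
3. **Other 6.1.1 parameters:** labelled secondary, as the Summary already does for most.
4. **Section 4.3:** say that the calculation concerns SIS mobility and that no power is claimed for LOS. Give instead the LOS SD that the sample can support: about 9.5 days or less for a 7-day difference with 30 per arm, two-sided 0.05 and 80% power. Add the lower ceiling for the 5-day average.
5. **HSU and RC/NH differences in LOS:** reported as estimates with confidence intervals.

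This needs wording only, with no added patients or visits. The price is one fewer route to claim success and a less favourable power statement. Keeping both outcomes primary at 0.025 each is not a mere wording change: on 4.3's own inputs, SIS mobility would then need 150 per arm.
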